#### Intervention

2.2.6

Following the obtention of the baseline data, the nurse who usually gives care to the patient will proceed to cure the venous ulcer using a standardized procedure. They will wash the area with saline solution and evaluate if mechanical debridement is necessary. Following, they will apply Cutimed Sorbact^®^ dressing (intervention) or Aquacel^®^ Ag Extra (control) dressings in the wound. Finally, they will cover the wound with a secondary gauze dressing and a double compression bandage. Patient's appointments will not extend beyond 72 hr, although depending on the level of exudate and the status of the wound, the nurse may decide to shorten this interval.

Dropout criteria are as follows: (a) Local or systemic clinical deterioration that indicates that continuation at the study is not appropriate; (b) Lack of patient's concordance; (c) Withdrawal of patient consent; and (d) Complete healing before week 12. The data collection period comprehends from May 2012 to December 2020.

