### Aim

2.1

The main aim of the study is to determine the effectiveness of a hydrophobic dressing (Cutimed Sorbact^®^) against a silver dressing (Aquacel^®^ Ag Extra) in the level of colonization of chronic venous leg ulcers.

The secondary aims will be to analyse the effect of Cutimed Sorbact^®^ versus Aquacel^®^ Ag Extra on total healing, the proportion of wound reduction, time of recovery, level of pain during recovery, and health‐related quality of life. In addition, the safety of Cutimed Sorbact^®^ will be evaluated.

The null hypothesis is that there is no difference in the level of bacterial colonization at 12 weeks of follow‐up in chronic ulcers treated with Cutimed Sorbact^®^ versus those treated with Aquacel^®^ Ag Extra.

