#### Sample

2.2.2

Assuming a 95% confidence level and 80% statistical power, 186 participants would be necessary (93 for each study arm) to detect a 20% load bacteria reduction (Mosti et al., 2015). This sample will be increased up to 204 participants to cover any possible patient dropouts.

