##### Primary endpoint

Level of colonization: it will be evaluated by quantitative real‐time polymerase chain reaction (qPCR) identification technique and quantified in CFUs and in nanograms (ng) of bacterial deoxyribonucleic acid (DNA) per μl of vascular ulcer exudate.

Two samples per wound (to have a reserve sample in case of possible contamination) will be collected by cotton swab directly from the wound bed. The samples will be collected before cleaning the wound to obtain a reliable microorganisms’ concentration. Swab tip will be rotated in a 1 cm^2^ wound surrounding area for 5 s. Next, cotton swabs will be placed in a sterile container at 4 ºC (Pugliese, 2016) until the process of qPCR.

Then, to determinate the total microorganisms’ quantity, samples will be subjected to a thermal shock, which consists in freezing them at −80ºC for 5 min, followed by heating samples at 95ºC for additional 5 min. With this procedure, gram‐positive and gram‐negative bacteria will be efficiently lysed. After spin centrifugation, DNA strands will be extracted for the following steps. The total DNA quantity of the isolated DNA will be measured using NanoDrop^TM^ spectrophotometer. Microorganisms will be quantitative determined by qPCR (referred to number of DNA copies amplified by this technique) (Rhoads, Wolcott, Sun, & Dowd, 2012).

Fast EvaGreen^®^ qPCR Master Mix (2X) kit will be used for qPCR amplification reactions, including specific primers usually present in vascular ulcers (Table 1; Etchebarne et al., 2017). Serial dilution will be performed from purified genomic DNA to generate a concentration calibration curve to compare data obtained from samples. From there, it will be possible to detect not only the presence of microbial species but also the quantitative determination of variation in these stains in samples of the same patient, as well as comparing treatments. Results will be standardized to CFUs per μL of exudate.

**Table 1 jan14412-tbl-0001:** Pathogen list usually founded and detected in vascular ulcers (Majewski et al., 1995) in addition to multi‐resistant pathogens (Moore et al., 2010)

Microorganism	Feature
*Staphylococcus aureus*	Commonly found on vascular ulcers
*Corynebacterium striatum*	
*Pseudomonas aeruginosa*	
*Helcococcus kunzii*	
*Proteus mirabilis*	
*Finegoldia magna*	
*Escherichia coli*	
*Staphylococcus aureus* methicillin/oxacillin resistant	Multi‐resistant pathogen described on vascular ulcers

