##### Secondary outcome measures

Wound size will be evaluated by planimetry using PictZar^®^ 7.6.1 software (Wendelken et al., 2011). Photos will be taken from affected area completely in parallel with respect to the ulcer and the photo will have to include a calibrated rule of 3 cm (standardized procedure according to PictZar^®^ planimetry). The characteristics and clinical evolution of the wound will be evaluated using the Resvech 2.0 scale (Restrepo‐Medrano & Verdú Soriano, 2011).

Healing time will be measured by the number of days until complete healing. This outcome will be complied if re‐epithelialization of the skin is confirmed in two consecutive visits across 2 weeks. Pain will be measured using the Numerical Rating Scale (NRS).

Health‐related quality of life will be measured by means of the Charing Cross Venous Ulcer Questionnaire (CCVUQ) (González de la Torre, Quintana‐Lorenzo, Perdomo‐Pérez, & Verdú, 2017; González‐Consuegra & Verdú, 2010). Adverse events related to the treatment will be collected both by nurses and patients. Follow‐up will be carried out at 4, 8, and 12 weeks, except the quality of life, which will be only evaluated at baseline and 12 weeks. Adherence to the treatment will be checked with the nurse and with the evaluation of consumed dressings.

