#### Data analysis

2.2.7

Data analysis will include descriptive statistics and exploratory analysis to determine the normality of the distributions and to check the range of data values. Bivariant analysis will be performed by chi‐square test, Student *t* test, Mann–Whitney U, Wilcoxon W, ANOVA, and Kruskal–Wallis test, depending on the normality of the distributions, type of variable analysed, and their homoscedasticity, which will be tested by the Levene's test. Intra‐group analysis will be performed by general linear models, with the corresponding corrections in multiple comparisons by Bonferroni test. To test the null hypothesis (inter‐group analysis), lineal generalized models will be developed in repeated measures, taking on consideration CFUs number as dependent variable as well as control or experimental designation group as a factor. Even if basal differences are significative, they will be attached as adjustment factor, following Mallinckrodt and Lipkovich recommendations (Mallinckrodt, Lipkovich, & Lipkovich, 2016). Sphericity will be tested using Mauchly test, Greenhouse‐Geisser test, or Huynh‐Feldt test in case of no setting.

All analyses will be performed by an intention‐to‐treat approach. To this purpose, missing data will be calculated by multiple imputation methods.

All the analyses will be performed in a blinded way.

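### Complete healing before week 12 is listed as a dropout, so healed ulcers have no week-12 load and, under standard multiple imputation, receive one drawn from ulcers still open

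*Protocol article*

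**What the plan says.** All places are in the protocol article.

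- **Intervention (2.2.6).** Four dropout criteria are listed. The last reads "d) Complete healing before week 12". The other three are clinical deterioration, lack of concordance and withdrawal of consent.
- **Aim (2.1).** "The null hypothesis is that there is no difference in the level of bacterial colonization at 12 weeks" of follow-up. Total healing and time of recovery are secondary aims.
- **Primary endpoint.** Two samples per wound "will be collected by cotton swab directly from the wound bed". Results are expressed as CFUs per microlitre of exudate.
- **Secondary outcome measures.** Healing requires re-epithelialisation confirmed at two consecutive visits across 2 weeks. Follow-up is at 4, 8 and 12 weeks, except for quality of life, "which will be only evaluated at baseline and 12 weeks".
- **Data analysis (2.2.7).** All analyses are by intention to treat. "To this purpose, missing data will be calculated by multiple imputation methods". No exception is made for healed wounds.
- **Sample (2.2.2).** 186 participants are needed, 93 per arm. "This sample will be increased up to 204 participants to cover any possible patient dropouts".

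**The concern.** A closed ulcer has no wound bed to swab and no exudate to quantify. Its week-12 load is absent because treatment succeeded, not because a visit was missed. The plan nevertheless files this success with withdrawal of consent and sends the gap to multiple imputation.

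At stake is the primary comparison. Every observed week-12 load comes from an ulcer that is still open. An imputation model that assumes data missing at random learns from those ulcers and gives the healed patient a colonised wound. If one dressing heals more ulcers, more of its best results are replaced in this way. The article's Discussion expects lower colonisation to lead to shorter healing times, so this is the benefit the trial hopes to see.

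Quality of life has one follow-up value, at week 12. A patient who leaves on healing has none.

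**Working it through.** **1. The plan's own sample size.** The Sample section gives 95% confidence, 80% power and a 20% reduction, but no SD, control rate or scale. So 93 per arm cannot be reproduced from its inputs alone. Two assumed readings return it:
- proportions of 50% vs 30%, two-sided 0.05, pooled variance, no continuity correction: 93 per arm;
- a standardised mean difference back-solved from 93 per arm with a two-sample t-test: d = 0.413.

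Both are assumptions, not figures of the trial.

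**2. The allowance.** 204 − 186 = 18, and 18/204 = 8.8%. Check: 93/(1 − 0.088) = 102 per arm, or 204. If 9% heal early, 0.09 × 204 ≈ 18, and nothing is left for other losses.

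**3. Patients with a week-12 swab.** With a share h healed and no other loss, 204 × (1 − h) remain. Power is for d = 0.413, or equally 50% vs 30%, using observed patients only:

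| h | with swab | power |
|---|---|---|
| 10% | 184 | 0.80 |
| 20% | 163 | 0.75 |
| 30% | 143 | 0.69 |
| 40% | 122 | 0.62 |
| 50% | 102 | 0.54 |

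The planned repeated-measures model would also use weeks 4 and 8, so these figures are a guide and not the trial's power.

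**4. Bias when the benefit acts only through healing.** Assume a mean week-12 log10 load of 5 in open ulcers of both arms, and an assigned value v in healed ulcers. With healing shares pT (test) and pC (control):

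difference with healed ulcers at v = (pT − pC) × (v − 5).

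- 50% vs 30%: 0.2 × (2 − 5) = −0.60 for v = 2, and 0.2 × (3 − 5) = −0.40 for v = 3. Simulation: −0.59 and −0.41.
- 40% vs 30%: −0.30 and −0.20. Simulation: −0.32 and −0.20.
- 40% vs 40%: 0.

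Multiple imputation from baseline load and arm, fitted on open ulcers, gives about 0 in every case. With unequal healing the benefit vanishes from the estimate. With equal healing there is no bias in this set-up.

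**5. Bias when the dressing lowers load in all patients.** Assumptions: four visits, autoregressive correlation 0.6, true week-12 difference 0.41 SD, healing when log10 load falls below a threshold, and sequential imputation within arm. The mean trend is also assumed. Share of the true effect retained (control/test healed):

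- *Only threshold crossings at visits before week 12:* 17%/24% leaves 88%; 25%/34% leaves 84%; 45%/55% leaves 78%. A further run gave about 82–92%. Overall, about 78–92%.
- *Ulcers closed at the week-12 visit also lost:* 8%/15% leaves 78%; 20%/31% leaves 66%; 38%/53% leaves 49%. A further run gave 43–70%. Overall, about 43–78%.
- *As the second, but healing depends on load plus noise (SD 1):* 18%/24% leaves 87%; 42%/52% leaves 77%.

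The first set is closest to criterion (d). Because healing must be confirmed across 2 weeks, closure must come by about week 10 to count before week 12. An ulcer closed at week 12 cannot be swabbed either, but criterion (d) does not cause that loss.

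**The case against.** **The imputation model is not described.** An analysis plan not shown could hold a rule for healed ulcers, so imputation from open ulcers is an inference. This stands as a limit on certainty. It does not remove the point: the article itself classes healing as dropout and sends missing data to imputation without exception. Nor can a later analysis rule recover quality-of-life data that were never collected.

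**Dropout may mean only the end of dressing use.** The criteria appear under Intervention, and nothing says that week-12 quality of life is not collected after healing. However, the deterioration criterion speaks of continuing in the study, and the Sample section treats dropouts as losses to be replaced. Leaving the study is the more natural reading.

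**Stronger readings a reader might infer.**
- *The comparison could reverse.* No simulation shows this: the sign is kept, or the estimate falls to about zero.
- *Losses are certain to exceed the allowance.* Without a healing rate, the documents support only that they may.
- *The deterioration and non-concordance criteria must be recast as well.* That is not needed to resolve the conflict over healing.

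**Scoring healed ulcers as the lowest load partly turns colonisation into a healing endpoint.** This is fair. In step 4 the 50% vs 30% result moves from −0.41 to −0.59 through the assigned value alone. The Discussion also says the dressings are meant to limit bacterial load, not eliminate it. The choice therefore needs justification and a sensitivity analysis.

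**Conclusion.** The point holds. As written, the dropout rule, the week-12 hypothesis, the swab-based endpoint and the imputation rule do not fit together. Following them would impute a wound load for patients whose wound has closed, and would lose their only follow-up quality-of-life value.

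Bias in the primary comparison is conditional. It needs unequal healing between arms, or different loads among those who heal. Where it arises, it may attenuate the result against the dressing that heals more. Time to healing is unaffected, because healing is its event.

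The documents do not fix the size. The retained shares of about 78–92% (healing before week 12 only) and about 43–78% (week-12 closures also counted) rest on the threshold model in step 5. Noise in healing makes the loss smaller. A benefit acting only through healing can disappear altogether. The power figures rest on an effect size back-solved from 93 per arm. The structural conflict rests on none of these assumptions.

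**What to change.** 1. Remove (d) from the dropout criteria and record complete healing as an outcome. Separate the end of dressing use from the end of follow-up. No treatment decision changes.
2. Keep healed patients in data collection to week 12 for quality of life, pain and adverse events.
3. Do not impute healed ulcers as open ones. Predefine how they enter the primary analysis, for example as the lowest load category with a rank-based analysis, plus a sensitivity analysis over the assigned value. Describe the estimand as composite.
4. Restrict multiple imputation to open ulcers with a missing swab.
5. State which losses the 18 extra patients are meant to cover.

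The cost is wording in the protocol and analysis plan, and one week-12 contact for each healed patient. The downside is a composite estimand that partly reflects healing and must be reported as such.

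### Early healing is classed as dropout and missing data are imputed without exception, so, as written, a closed ulcer would receive a modelled week-12 bacterial count

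*Protocol article*

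**What the plan says.** Four statements in the protocol article bear on this point.

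- **Aim.** The null hypothesis is that "there is no difference in the level of bacterial colonization at 12 weeks".
- **Primary endpoint.** Colonisation is measured by qPCR on a swab taken from the wound bed and is expressed per microlitre "of vascular ulcer exudate".
- **Intervention.** "Complete healing before week 12" is the fourth dropout criterion. The other three are clinical deterioration, lack of concordance and withdrawal of consent.
- **Data analysis.** All analyses are by intention to treat, and for that purpose "missing data will be calculated by multiple imputation methods". Healing is not excepted. The primary model is a repeated-measures model of the bacterial count by group.

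Healing itself is a secondary outcome. Under Secondary outcome measures it is the number of days to complete healing, with closure confirmed at two consecutive visits across two weeks. The same section schedules quality of life at baseline and week 12 only. The Sample section says: "This sample will be increased up to 204 participants to cover any possible patient dropouts".

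**The concern.** An ulcer that has re-epithelialised has no wound bed to swab and no exudate. Its week-12 count is not an unobserved number; it does not exist. If healing is dropout and everything missing is imputed, the best outcome in the trial enters the primary comparison as a count typical of an open ulcer. The estimate then answers a hypothetical question (the load had the ulcer not healed) while being reported as colonisation at 12 weeks.

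The article's own premise makes this more than a matter of labels. The Background says that a high load impairs healing, and the Discussion presumes that lower colonisation shortens healing time. Healing is therefore tied to the primary outcome and should not be handled like a withdrawal of consent. Swabs are planned only at weeks 4, 8 and 12, so the load just before closure will often be unmeasured. Standard multiple imputation assumes that missingness depends only on observed data, and here it plausibly does not.

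A second loss follows if dropout means leaving the study. A patient who heals and leaves before week 12 has no quality-of-life value after baseline, although one could be collected. A reopening before week 12 would also go unrecorded.

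**Working it through.** **1. The plan's own figure.** The Sample section gives 186 (93 per arm) "to detect a 20% load bacteria reduction", raised to 204. It gives no baseline rate or SD, so 93 cannot be derived from its inputs alone. If the reduction is read as 50% v 30% (assumption), with two-sided 5% and 80% power, the pooled formula gives

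n = [1.96√(2×0.40×0.60) + 0.8416√(0.50×0.50 + 0.30×0.70)]² / 0.20² = (1.358 + 0.571)² / 0.04 = 93 per arm.

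The dropout allowance is 204 − 186 = 18, and 18/204 = 8.8%. The point made here does not depend on how 93 was obtained.

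**2. The chain of rules.** Hypothesis at week 12 → value needs a wound-bed swab → a closed ulcer cannot be swabbed → closure is dropout → missing data are imputed, no exception. The week-12 count of a healed ulcer can then come only from the imputation model, whose week-12 information comes from ulcers still open.

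**3. How many values.** No healing rate is given, so a range is assumed.

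| Healed before week 12 (assumed) | Week-12 values without a swab, of 204 | Still open |
|---|---|---|
| 10% | 20 | 184 |
| 20% | 41 | 163 |
| 30% | 61 | 143 |
| 40% | 82 | 122 |
| 50% | 102 | 102 |

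Even 10% healing exceeds the allowance of 18 before any other loss.

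**4. What the two treatments of healing estimate.** Suppose 50% of open ulcers are colonised in both arms, and 40% v 20% heal. Imputing healed ulcers from open ones targets 50% v 50%, a difference of 0. Counting a healed ulcer as not colonised gives 0.50×(1 − 0.40) = 30% v 0.50×(1 − 0.20) = 40%, a difference of −10 points. With 20% healing in both arms the second approach gives 40% v 40%, also 0.

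**5. Simulation.** Assumptions: 102 per arm; log10 counts with means 6.0, 5.6 and 5.2 at baseline, week 4 and week 12; between-patient and residual SD 0.6 each; no difference in open-ulcer load; healing likelier at lower week-4 count; 10 imputations from arm, baseline and week-4 count; baseline-adjusted comparison at week 12; 400 trials per row.

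| Healed, arm A v arm B | Imputed: difference (log10) | Imputed: rejects | Healed = not above 10^5: difference (points) | Rejects | Closed ulcers imputed above 10^5 |
|---|---|---|---|---|---|
| 20% v 20% | 0.002 | 5.5% | 0.0 | 3.2% | 47% |
| 30% v 20% | −0.001 | 8.0% | −5.6 | 10.5% | 49% |
| 40% v 20% | −0.006 | 4.2% | −11.6 | 38.2% | 50% |
| 50% v 30% | −0.004 | 6.5% | −11.2 | 31.8% | 51% |
| 30% v 10% | −0.003 | 6.2% | −10.6 | 35.8% | 48% |

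The standard error of a 5% rejection rate over 400 trials is √(0.05×0.95/400) = 1.1 points. The last column depends on the assumed means. Healing here depends on an observed count, so these runs do not show the further bias that arises if it depends on unswabbed load; I put no figure on that.

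**6. The price of scoring healing as cleared.** In a second simulation (102 per arm, log10 SD 1, within-patient correlation 0.6, load 0.3 log10 lower in one arm), healing of 31% v 33% gives power of 60% with imputation and 21% with healed ulcers ranked lowest. Healing of 31% v 45% gives 53% with imputation and 70% to 79% with healing scored as cleared.

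**The case against.** The strongest reply is that the imputation of healed ulcers is an inference. No sentence states it, the imputation model is not specified, and a fuller protocol or SAP could code closure separately. That is right, and it is why the point is worded as what follows from the rules as written. It does not dispose of the point: the article does not leave healing open but places it among the dropouts, and it states one rule for missing data.

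The primary aim is also microbiological, and healing is assessed as a secondary outcome. On that view an estimate near 0 with rejection close to 5% in step 5 is correct behaviour when open-ulcer load is equal. This stands: those runs show that the imputed analysis is blind to healing, not that it is invalid for a load question. The difficulty is that the question it answers is not the one stated. The simulated model is also simpler than the planned repeated-measures model.

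A reader might infer more than the documents support:

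- *That healing earns no credit at all.* Low counts at weeks 4 and 8 can pull the imputed values down.
- *That the wound area of healed ulcers would be imputed as open.* Closure is confirmed directly at two visits, and nothing says that a known area of 0 would be replaced.
- *That the result is biased against one dressing.* No healing rate is given for either arm, and with equal healing the simulated difference stays near 0.
- *That healed ulcers must be ranked lowest in the primary analysis.* That makes the endpoint a composite of healing and load, and step 6 shows that it can cost much of the power.

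**Conclusion.** The point holds as a badly fixed rule. Read together, the Intervention and Data analysis sections turn a confirmed good outcome into missing data and fill it with a count that cannot exist. The primary estimate would then describe a hypothetical load without saying so.

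The number of values affected is about 20 to 102 of 204, resting on an assumed 10% to 50% healed; the comparison with the allowance of 18 uses the article's own figures. The distortion between arms is unknown. It is expected mainly if healing differs by arm or depends on load that was not swabbed, and may be close to nothing otherwise. The loss of the week-12 quality-of-life value does not depend on any difference between arms, but it does assume that dropout ends follow-up.

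**What to change.** 1. **Intervention section.** Remove complete healing from the study dropout criteria. Healed patients stay in follow-up to week 12, with ulcer status and quality of life recorded. This concerns follow-up only, not treatment.
2. **Data analysis section.** Restrict multiple imputation of the count to ulcers that are still open but were not swabbed.
3. **Healing as an intercurrent event.** Prespecify the strategy before unblinded data are seen. One option is a composite in which confirmed closure is scored as not colonised, reported with the load in open ulcers, the number of open ulcers and the proportion healed in each arm. Whether the composite is primary or supportive is the sponsor's choice.
4. **Wound area.** Confirm that area 0 and 100% reduction are entered as observed values for confirmed closures.

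The cost is wording in the protocol and SAP, plus a week-12 status check and questionnaire for healed patients, without a swab. If the composite is made primary, the further cost is power when load falls without a difference in healing.
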